#### Outcomes

### Feasibility outcomes

Feasibility outcomes will be measured at the end of the 4-week treatment period.The proportion of participants assessed for eligibility who consent to inclusion and randomizationWe will compare the number of eligible participants to the number of randomized participants. We will accept a difference above 50% (95% CI 40.2% to 59.6%). A larger difference can impose difficulties with recruitment in a future randomized trial.Compliance with the interventionWe will calculate the number of participants fulfilling treatment for both the group receiving sham and active eTNS. Compliance with treatment will be defined as completing the treatment in 70% (95% CI 58.4% to 81.6%) of the nights during the four weeks. Abruption of treatment can only be accepted if it happens within less than four nights in a row.Acceptability of the interventionThe acceptability of the intervention will be assessed using a semi-structured qualitative interview guide with predefined questions:How did you feel about administering and controlling the device?How did your child feel about receiving this type of treatment?How was it for your child to receive home-treatment with the device in addition to other strategies provided by the clinic?Did the intervention have any influence on the relationship between your child and the parents/siblings/school/friends?Completion of follow upCompletion of follow-up will be defined as completing the assessment of the primary exploratory clinical outcome at the end of the intervention. The number of participants with completed outcomes will be compared to the number of participants in total. If the number of participants completing this assessment is above 90% (95% CI 82.4% to 97.6%), this will be acceptable for a future full-size trial. If the number of participants completing the assessment is below 75%, this will introduce serious problems with the interpretation of the results.Use of concomitant treatmentAny concomitant treatment or changes in medication will be assessed for each participant and subsequently evaluated for the two groups at the end of the trial.

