## Abstract

External trigeminal nerve stimulation (eTNS) is a non-invasive technique involving external cutaneous stimulation of the trigeminal nerve. In 2019, the Monarch eTNS device was approved as a treatment for children with attention-deficit/hyperactivity disorder (ADHD). The Monarch eTNS device is designed to be applied at home, which offers a certain level of convenience but also necessitates a high degree of compliance and acceptability from the families. To assess the feasibility of – and pilot a larger randomized clinical trial investigating the Monarch eTNS device versus sham for patients aged 7 to 17 years with ADHD. We will conduct a parallel-group, sham-controlled, feasibility randomised clinical trial. We will include 60 children and adolescents (aged 7 to 17 years) diagnosed with ADHD from three clinical sites in Denmark. Patients will be randomised to 4 weeks of active versus sham eTNS. Feasibility outcomes include completion of the trial; the number of eligible participants who consent to inclusion; treatment compliance; acceptability of the intervention and completion. Adverse events will be monitored throughout the trial. Exploratory clinical outcomes include ADHD core symptoms (primary) and several secondary outcomes. Autonomic functions will be evaluated by means of heart rate variability, using a heart rate sensor. This trial will allow us to evaluate the feasibility of conducting a larger randomised clinical trial investigating the use of eTNS as a home-based, non-pharmacological intervention for children and adolescents diagnosed with ADHD.

Trial registration: ClinicalTrials.gov ID: NCT06655610. Registered 23.10.2024.

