### Participant timeline

Eligible participants will be identified by clinicians working at the respective trial sites. They will ask the families whether they are willing to be contacted by the trial researchers for further information. The trial researcher will send a letter of information and request permission to follow-up with a phone call. Following the phone call, an in-person meeting will be scheduled, in which both oral and further written information will be provided. If the families wish to participate, a second in-person meeting is scheduled. At this second meeting, informed consent is obtained as well as a standard diagnostic—and health evaluation alongside baseline assessment and HRV measurements. The child is finally included in the trial, granted they meet the inclusion criteria following the health – and diagnostic evaluation. Randomisation then commence, in which the participant is allocated to either active or sham eTNS.

They will then proceed to test the device for four weeks. Families will keep a logbook for daily reporting on how the previous night had gone by. Once a week, they will fill in an online questionnaire received by email related to the primary exploratory outcome and the reporting of any adverse events. This email will also contain questions regarding the use of the device and concomitant medication. In addition, the families will receive a weekly phone call from the trial researcher, to remind them to fill in the questionnaire and to allow the families to ask questions if needed. Families may also contact a trial researcher directly via phone throughout the trial period.

Following the four weeks, an in-person meeting is scheduled, in which the families and trial investigators meet to discuss and share their experience. During this meeting, exploratory outcomes will once again be assessed, alongside HRV measurements and the rating of any adverse events. The full participant timeline is seen in Fig. 1.

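### The recruitment criterion has two denominators and two meanings of eligible, so the same counts can pass or fail its 50% threshold

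*Protocol article*

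**What the plan says.** Three places in the Protocol article describe the recruitment outcome.

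- **Feasibility outcomes, title of the outcome:** the "proportion of participants assessed for eligibility who consent to inclusion" and randomisation. The denominator is everyone assessed.
- **Feasibility outcomes, next sentence:** the investigators "will compare the number of eligible participants to the number of randomized participants". The denominator is the eligible.
- **Abstract:** "the number of eligible participants who consent to inclusion", given as a count.

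The threshold is 50%, with a printed 95% interval of 40.2% to 59.6%.

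The Participant timeline begins before any researcher contact: "Eligible participants will be identified by clinicians working at the respective trial sites". Information by letter, phone and a first meeting follows. Only families who wish to take part reach a second meeting: "At this second meeting, informed consent is obtained as well as a standard diagnostic" and health evaluation, with the baseline assessment. Inclusion and randomisation follow if the criteria are met. The Participants section separates potential from final eligibility, and Inclusion criteria lists signed consent among the criteria.

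**The concern.** Assessed and eligible children are different groups, because the second excludes screen failures. In addition, *eligible* can refer to a stage before consent or to one reached only after it. These denominators sit at different points of the recruitment funnel, and families who decline are visible from some of those points and not from others.

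This bears on a stated aim. The Discussion says the trial will show whether the recruitment strategy is adequate, and reports that recruitment to the preliminary study was held back because families needed immediate support. Families lost for that reason may well leave before the second meeting. A denominator formed at or after that meeting would not count them. The Background makes the full-size trial depend on feasibility being shown.

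Timing adds to the problem. Data analysis promises the detailed SAP before the last participant is randomised. Nearly all recruitment counts could be known by then, and blinding to allocation does not hide them.

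**Working it through.** **Step 1. Does the printed interval reveal the intended denominator?** The Wald interval is p ± 1.96 × √(p(1−p)/n). It reproduces the other two feasibility intervals with n = 60:
- compliance: 0.70 ± 1.96 × √(0.21/60) = 58.4% to 81.6%
- completion: 0.90 ± 1.96 × √(0.09/60) = 82.4% to 97.6%

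For recruitment at p = 0.50:

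| n | Wald 95% interval |
|---|---|
| 60 | 37.3% to 62.7% |
| 100 | 40.2% to 59.8% |
| 120 | 41.1% to 58.9% |
| *printed* | *40.2% to 59.6%* |

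None matches exactly. The Wilson interval with n = 100 gives 40.4% to 59.6%, and no Wald, Wilson or Clopper-Pearson interval tried with n from 90 to 124 reproduced both limits. The nearest denominator is about 100. Yet 60 randomised (Sample size and power consideration) at 50% implies 60/0.50 = 120. The interval does not identify the group meant.

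**Step 2. When is eligibility settled?** Final eligibility needs signed consent and a baseline ADHD-RS total above 24 (Inclusion criteria). Consent and the baseline assessment both belong to the second meeting (Participant timeline). A child confirmed as eligible has therefore already consented, and randomisation is the next step.

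**Step 3. Three denominators.** Let A be children identified and approached, c the share who consent, e the share of consenters confirmed eligible, and r the share of those randomised. Take *assessed* to mean evaluated at the second meeting. Then:
- randomised / approached = c × e × r
- randomised / assessed = e × r
- randomised / confirmed eligible = r

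Only the first contains c, so only the first responds to families declining.

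**Step 4. Illustration.** The article gives no funnel rates. I assume e = 0.70 to 0.90 and r = 0.95 to 1.00, so e × r runs from 0.70 × 0.95 = 0.665 to 0.90 × 1.00 = 0.90.

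| Assumed consent c | / approached | / assessed | / confirmed eligible |
|---|---|---|---|
| 10% | 6.7–9.0% | 66.5–90% | 95–100% |
| 50% | 33–45% | 66.5–90% | 95–100% |
| 70% | 46.5–63% | 66.5–90% | 95–100% |

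Read as requiring randomised/denominator above 50%, the approached version passes only if c exceeds 0.50/(e × r). That is between 0.50/0.90 = 56% and 0.50/0.665 = 75%. Under these rates, the verdict depends on the denominator if consent is below about 56%, may depend on it between 56% and 75%, and does not depend on it above 75%.

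**The case against.** A reader might infer that the criterion is near 100% by construction and cannot detect a recruitment problem. The article does not support that as a general statement. It calls clinician-identified children eligible before any researcher contact, and the Abstract's wording places eligibility before consent. Consent is the event being counted, which would be pointless if everyone in the denominator had already given it. A 50% threshold, with an interval implying about 100 in the denominator, also suggests that the authors expected substantial non-uptake. On that reading the criterion moves with refusals and can fail. All this stands, and it limits the near-100% result to the confirmed-eligible reading.

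Three further objections have weight. The funnel rates are assumed, and at high consent the verdict need not change. The only numerical rule tied expressly to proceeding is 90% completion; for recruitment the article says only that "A larger difference can impose difficulties with recruitment in a future randomized trial". Raw counts at each stage could still be reported whatever the label.

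It can also be said that stage definitions belong in the full protocol or SAP. That would answer an omission, but here the article states two denominators that disagree.

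**Conclusion.** The point holds as an undefined denominator. The recruitment outcome names two denominators, and *eligible* is used for stages before and after consent. The pre-consent reading is the more natural one and can detect poor uptake. The confirmed-eligible reading is permitted by the text and is uninformative about refusals. The assessed reading shares that weakness if assessment means the second-meeting evaluation.

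At an assumed 50% consent, the criterion fails against approached children (33–45%) and passes against assessed (67–90%) or confirmed eligible (95–100%). These figures rest on assumed rates of confirmation (70–90%) and randomisation (95–100%), and on reading the rule as a minimum proportion of 50%. This should be fixed, but it does not undermine the trial.

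That last assumption is needed because the article says it accepts a difference above 50% and then treats a larger difference as a difficulty. This is a separate slip in direction that the same edit can correct.

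**What to change.** Before the recruitment counts are known:

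1. State one numerator, children randomised, and one pre-consent denominator: children whom site clinicians identify as potentially eligible and who are approached, taken from the screening log.
2. Confirm that 50% is meant for this proportion, since the authors may have had another in mind, and apply it there only. Word it as a minimum proportion rather than a difference.
3. Report the step proportions beside it: agreed to contact / approached, consented / informed, and eligible / consented.
4. Use the same wording in the Abstract, Feasibility outcomes and Participant timeline, and keep *potentially eligible* and *confirmed eligible* as separate terms.

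The cost is a change of wording in the protocol or SAP and a screening log kept from the point of identification. The downside is that the reported proportion may look less favourable than one formed after consent.

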### Sample size and power consideration

We will include 60 participants which corresponds to approximately 20% of the sample size needed for the full-scale randomized superiority trial. This corresponds to a power of 48% for the primary outcome (ADHD core symptoms) in this feasibility trial, indicating that the risk of type 1 error is high, and any finding thus may only be considered as exploratory.

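### The recruitment feasibility criterion contradicts itself: it accepts a difference above 50% between eligible and randomised participants, then calls a larger difference a problem

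*Protocol article*

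**What the plan says.** The Protocol article, under Feasibility outcomes, lists recruitment first. The title of the outcome is a proportion: those who consent and are randomised, out of those assessed for eligibility. The text below it compares the count of eligible participants with the count randomised and gives the rule: "We will accept a difference above 50% (95% CI 40.2% to 59.6%). A larger difference can impose difficulties with recruitment".

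Two other feasibility outcomes in the same section carry a percentage with an interval. For completion of follow-up: "If the number of participants completing this assessment is above 90% (95% CI 82.4% to 97.6%), this will be acceptable for a future full-size trial". For compliance, a participant is compliant after "completing the treatment in 70% (95% CI 58.4% to 81.6%) of the nights during the four weeks".

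Sample size and power consideration gives the planned size: "We will include 60 participants which corresponds to approximately 20% of the sample size needed for the full-scale randomized superiority trial".

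Participant timeline describes the route into the trial. Clinicians at the sites identify eligible participants; contact, written information, a phone call and an information meeting follow. At a second meeting "informed consent is obtained as well as a standard diagnostic" and health evaluation, and randomisation comes after that.

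No other section gives a recruitment threshold. The Discussion says only that the trial will show whether the recruitment strategy is adequate.

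**The concern.** The sentence that sets the rule accepts large differences, and the sentence that justifies it treats large differences as harmful. Both cannot hold for the same quantity. Feasibility is the only stated objective (Objective), and the Background makes the full-sized trial depend on it. Recruitment is also a known risk, since the Discussion reports that it was hindered in the preliminary study. A published threshold for this outcome should not have to be interpreted after the data are in.

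Two smaller matters affect the same criterion. The title and the text name different denominators (assessed for eligibility, and eligible). The interval printed beside 50% also does not look like an interval around 50%.

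**Working it through.** **1. Direction of the rule**

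Inputs: 60 randomised (Sample size and power consideration); threshold 50% (Feasibility outcomes). The numbers eligible below are illustrations, because the protocol does not give one.

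Uptake u = randomised / eligible. Difference d = 1 − u.

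Rule as printed: accept if d > 50% ("We will accept a difference above 50"). Rule implied by the title of the outcome: accept if u > 50%, which is the same as d < 50%.

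| Eligible | Uptake u | Difference d | As printed (d > 50%) | As a proportion (u > 50%) |
|---|---|---|---|---|
| 300 | 20% | 80% | accepted | not accepted |
| 200 | 30% | 70% | accepted | not accepted |
| 150 | 40% | 60% | accepted | not accepted |
| 120 | 50% | 50% | not accepted | not accepted |
| 100 | 60% | 40% | not accepted | accepted |
| 75 | 80% | 20% | not accepted | accepted |

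Except at exactly 50%, the two rules give opposite answers. The printed rule also opposes its own rationale: "A larger difference can impose difficulties with recruitment in a future randomized trial".

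There are two ways to read the text. If difference means the shortfall between eligible and randomised, then above should be below. If the proportion randomised was meant, above is right and difference is the wrong word. Both readings lead to the same corrected rule, u > 50%.

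**2. The attached interval**

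Wald 95% interval: p ± 1.96 × √(p(1 − p)/n).

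The other two printed intervals reproduce with n = 60:

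- p = 0.70: 1.96 × √(0.21/60) = 0.116, giving 58.4% to 81.6%, as printed.
- p = 0.90: 1.96 × √(0.09/60) = 0.076, giving 82.4% to 97.6%, as printed.

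The recruitment interval, 40.2% to 59.6%, does not reproduce:

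- Its arms are 50 − 40.2 = 9.8 points and 59.6 − 50 = 9.6 points. A Wald interval around 50% has equal arms.
- Wald, n = 60: 37.3% to 62.7%. Neither limit matches.
- Wald, n = 100: 1.96 × √(0.25/100) = 0.098, giving 40.2% to 59.8%. Only the lower limit matches.
- Wilson, n = 100: 40.4% to 59.6%. Only the upper limit matches.
- Wald, n = 120 (60 randomised at 50% uptake): 1.96 × √(0.25/120) = 0.0895, giving 41.1% to 58.9%. Neither limit matches.

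A search over every count for n from 60 to 139 with the Wald, Wilson, Clopper-Pearson, Agresti-Coull and Jeffreys methods found no case that gives both printed limits.

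**3. The denominator**

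The title counts those assessed for eligibility and the operative sentence counts those eligible. Participant timeline uses the word eligible for patients whom clinicians identify before any contact, while the criteria are confirmed only at the second meeting. The two terms can therefore refer to different groups.

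**The case against.** The strongest reply is that this is a slip whose meaning can be recovered. The title says proportion, and the completion criterion uses above for a good result. If proportion replaces difference in the acceptance sentence, the next sentence still makes sense as a remark about the gap between eligible and randomised. Nobody who reads the whole paragraph would pass 60 of 300 and fail 60 of 100. That reply stands as to intent, and the point is therefore an internal contradiction and not a poor choice of design. It does not remove the contradiction, because the threshold is stated once and is reversed where it is stated.

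Three stronger readings are tempting and are not supported.

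- **That uptake would be near 100% by construction**, because diagnostic evaluation and consent share a visit. Participant timeline has clinicians identify eligible participants before contact, so the denominator may well be the pre-consent pool. After consent, children can still fail the diagnostic interview, the ADHD-RS threshold or an exclusion criterion, and no screen-failure rate is given.
- **That missing 50% formally stops the programme.** The protocol ties completion expressly to going ahead with a larger trial. For recruitment it speaks only of possible difficulties.
- **That the interval must use n = 120.** That figure assumes exactly 50% uptake, and the protocol does not fix the number eligible. The simplest explanation of the printed upper limit is a slip for 59.8%, with a denominator of 100 that is not stated.

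A screening log and counts at each recruitment step are details that a condensed article may leave to the full protocol, so their absence is not part of this point.

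**Conclusion.** The point holds as an internal contradiction in a stated feasibility threshold. As printed, uptake of 20% to 40% is accepted and uptake of 60% or more is not. The likely intended rule, a proportion randomised above 50%, gives the reverse. With 60 randomised, that rule means fewer than 120 eligible participants. The contradiction itself needs no assumption about the number eligible. The inference about intent rests on the outcome's title and the parallel completion criterion.

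The interval is a minor error: its upper limit is 0.2 points from the Wald value for n = 100, and its denominator is not stated. The mixed denominator terms are an ambiguity to settle in the same edit. They do not show that the measure would be uninformative.

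**What to change.** Replace the acceptance sentence and the one after it with a rule in the direction of the title: recruitment is acceptable if the proportion of eligible participants who are randomised is above 50%, and a lower proportion signals difficulty for a later trial. Keep the threshold strict, as now.

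Use one denominator term in title and text and define it, for example the eligible participants identified by clinicians before consent, as Participant timeline describes.

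Restate the interval with its method and assumed denominator: Wald 40.2% to 59.8% if n = 100 was meant, or 41.1% to 58.9% if n = 120 (60 randomised at 50% uptake).

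The cost is a correction to a few lines of the protocol, carried into the statistical analysis plan. It needs no extra participants, visits or data, and is best made before the recruitment figures are assessed.

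### The recruitment criterion contradicts itself: it accepts a gap above 50% between eligible and randomised participants, then calls a larger gap a problem

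*Protocol article*

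**What the plan says.** Under Feasibility outcomes, the first outcome is labelled as a proportion: the share of those assessed for eligibility who agree to take part and be randomised. The text then says that the number eligible will be set against the number randomised, and gives the criterion: "We will accept a difference above 50% (95% CI 40.2% to 59.6%). A larger difference can impose difficulties with recruitment". The warning sentence reads in full: "A larger difference can impose difficulties with recruitment in a future randomized trial".

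The same section words its completion criterion in the expected direction: "If the number of participants completing this assessment is above 90% (95% CI 82.4% to 97.6%), this will be acceptable". The planned number randomised comes from the section on sample size and power: "We will include 60 participants which corresponds to approximately 20% of the sample size needed".

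No other section gives a recruitment threshold. The Discussion says only that the trial will show whether the recruitment strategy is adequate.

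**The concern.** After a comparison of eligible with randomised participants, a *difference* most naturally means the share lost between the two. A rule that accepts a difference above 50% then accepts the loss of more than half, and the next sentence treats movement in that same direction as a difficulty. Both sentences cannot hold.

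Feasibility is the only stated objective of this trial, and the Background makes a full-sized trial conditional on it. Recruitment is also a known risk: the Discussion reports that it was hindered in the preliminary study and that patients on stable medication are now included in the hope of improving it. An acceptance threshold set in advance is meant to stop the verdict being chosen after the data are seen. With two conflicting sentences, one or the other could be cited for either verdict.

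**Working it through.** **Inputs.** Planned number randomised: 60 (Sample size and power consideration). Threshold: 50% (Feasibility outcomes). Number eligible, *E*: not given, so the values below are assumptions. The difference is taken as a percentage of the number eligible.

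**The plan's own figures.** The intervals attached to the other two thresholds reproduce as p ± 1.96 × √(p(1 − p)/n) with n = 60:
- 70%: 0.70 ± 1.96 × √(0.70 × 0.30/60) = 0.70 ± 0.116, or 58.4% to 81.6%, as stated.
- 90%: 0.90 ± 1.96 × √(0.90 × 0.10/60) = 0.90 ± 0.076, or 82.4% to 97.6%, as stated.
- 50%: the same formula gives 37.3% to 62.7%, not the stated 40.2% to 59.6%. With n = 100 it gives 40.2% to 59.8%, which matches the lower limit only.

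The recruitment interval is therefore not reproduced. That is a separate matter. An interval around 50% cannot show whether the share randomised or the share lost was meant, because at 50% the two are equal.

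**The two sentences under each meaning of *difference*.**

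| Meaning | Acceptance sentence | Warning sentence |
|---|---|---|
| Share lost | Accepts losing more than half: wrong direction | Sensible |
| Share consenting | Sensible | Says that higher consent hinders recruitment: wrong direction |

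Either way, one sentence has to change.

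**The acceptance sentence taken alone.** Share randomised = 60/E and share lost = (E − 60)/E. The share lost exceeds 0.5 when E − 60 > 0.5E, that is, when E > 120.

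| Assumed E | Randomised | Lost | Acceptance sentence alone (lost > 50%) | Restated rule (randomised > 50%) |
|---|---|---|---|---|
| 75 | 80.0% | 20.0% | fails | passes |
| 100 | 60.0% | 40.0% | fails | passes |
| 119 | 50.4% | 49.6% | fails | passes |
| 120 | 50.0% | 50.0% | fails | fails |
| 121 | 49.6% | 50.4% | passes | fails |
| 200 | 30.0% | 70.0% | passes | fails |
| 600 | 10.0% | 90.0% | passes | fails |

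The two rules disagree everywhere except at exactly 50%, where neither strict inequality is met. If the restated rule said *at least 50%*, they would disagree there too.

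**Sampling variation.** Suppose eligible participants are approached until 60 are randomised. Then E > 120 is the same event as fewer than 60 randomised among the first 120 eligible. The acceptance sentence alone would pass with probability 0.983 if the true share randomised is 40%, 0.464 if it is 50%, and 0.0105 if it is 60%. These true shares are assumptions, and the figures describe that one sentence only. The criterion as a whole contradicts itself and so has no defined operating characteristics.

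**The case against.** The strongest reply is that nobody would apply the acceptance sentence literally. The outcome label describes a proportion for which higher is better, the warning sentence says that a larger gap is bad, and the completion criterion uses *above* for a favourable result. All three point to more than half being randomised. The counts needed to judge recruitment will be collected however the sentence is read, and no clinical-outcome analysis is touched.

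Most of this stands. It shows that the intent is recoverable and that the error is probably one of drafting. It does not make the published criterion usable, because a reader still has to decide which sentence to disregard. Nor is this detail that an article leaves to a fuller document: the threshold and its direction are stated, and stated inconsistently.

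A reader might infer two stronger things that the documents do not support. The first is that the rule is simply reversed, so that the investigators would pass failed recruitment. The warning sentence says the opposite, so the rule is self-contradictory rather than reversed. The second is that a wrong decision on the full-sized trial would follow. The Background ties that trial to feasibility in general. The explicit threshold for proceeding is the 90% completion rate, and no formal stop/go rule is attached to recruitment.

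**Conclusion.** The point holds as an internal contradiction in a stated acceptance threshold. Whichever meaning *difference* is given, one of the two sentences is wrong, and no other section of the protocol article settles the direction. This conclusion rests on the text alone and needs no assumption.

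The size rests on the planned 60 randomised and on assumed numbers eligible: taken alone, the acceptance sentence fails 60 of 75 and passes 60 of 200, the reverse of the evident intent. The correction is worth making before results are seen, because recruitment is one of the few feasibility outcomes with a numerical acceptance threshold. The evidence points to a wording error, not to an intention to accept poor recruitment.

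**What to change.** Restate the criterion as a proportion and keep the plan's own threshold and strict inequality, for example:

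*Recruitment is acceptable if more than 50% of eligible participants are randomised (that is, fewer than 50% are lost between eligibility and randomisation); a larger loss indicates recruitment difficulties for a future trial.*

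If the sponsor prefers *at least 50%*, that moves the boundary case and should be a stated choice.

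Two neighbouring points are separate and for the sponsor to settle: whether the denominator is those assessed for eligibility (as in the label) or those eligible (as in the comparison), and how the stated interval of 40.2% to 59.6% was obtained. The example uses eligible participants only because the comparison sentence does.

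The cost is one sentence. It can go into the detailed statistical analysis plan, which the Data analysis section promises before the last participant is randomised. No additional data and no change for participants are needed.
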